#### Sample size and sampling

In-depth and free-listing interviews will be conducted with adolescents (n=20), caregivers (n=20), HCPs (n=20) and four (n=8) participatory group discussions, two with adolescents and one with caregivers and HCPs, respectively. Participants in the free listing interviews will be invited to participate in the in-depth interviews. All participants will be purposefully chosen.

The inclusion criteria are as follows:

Adolescent participants: (1) living with HIV; (2) aged 16–19 years at the time of recruitment; (3) residence in uMkhanyakude district at the time of diagnosis and treatment; (4) who know their status; (5) in active care at one of the HIV clinics within the AHRI ACDIS and (6) willing and able to consent to participate. Potential adolescents will be excluded if they are unaware of their status and those with self-reported history of severe mental illness.Caregivers: These will be identified by adolescent participants as primary caregivers, significant others or prominent supporters and will be recruited through nomination by the adolescent patient.Clinician/health and social care professional participants must be nominated by adolescent participants from recruiting clinics and community-based organisations.

#### Study procedures

ALHIV will be identified from the HIV clinics in the AHRI database (ACDIS). With the help of AHRI research nurses and clinic research assistants, we will introduce the study to them and seek their consent. Adolescents’ HIV status will be checked against their clinical records. For those who consent to participate, the ALHIV will be interviewed separately from their caregiver unless the adolescent requests their presence during the interview. HCPs working with ALHIV will be recruited from participating health centres. Participatory group discussions and interviews will be conducted in a private room within the health clinics, and each group will be invited to participate on separate days. Participants in the free listing exercise will be invited to participate in the interviews.

#### Data analysis

An intervention-mapping framework and realist principles will inform the coding process that [name] and NN will lead. Thematic and narrative analyses will be conducted using a predeveloped programme theory. Part of the synthesis will involve identifying the weighting of existing subdomains and the polarity of the constructs to show how they interact and influence other health constructs. The interviews of caregivers and professionals will focus on the concepts of interest concerning the young person living with HIV, adherence and mental health. The interviews with HCPs will focus on their perspectives on adherence challenges and experiences in caring for this ALHIV population. The information gathered through these interactions will be used to develop an outcome-focused programmed theory to investigate the underlying causal mechanisms of mental health problems among ALHIV. The model will be interrogated as more data are collected to refine and clearly describe causal processes and identify any mediators of these causal influences. The gathered data will also be used to identify behavioural strategies of adherence commonly used by adolescents and to explore the gender and potential age differences that might need to be considered in the intervention.

### Phase 2: deep structure adaptions of PM+Adherence

With the findings from phase 1, we hope to understand how ALHIV make sense of their illness and how they navigate the associated challenges, including mental health and psychosocial issues. We will then use this information to adapt the intervention components purposefully.

#### Adaptation workshop

Three iterative adaptation workshops will be conducted with mentors and stakeholders (ALHIV, n=10) and healthcare providers (n=8) to review all the findings from phase one to determine recommendations for adaptation as well as the adherence components that will be incorporated into the adapted version. The identified recommendations will be compiled for suggested adaptations to intervention materials, training materials or implementation considerations. They will be coded according to the Bernal framework for cultural adaptation of psychological interventions.^65^,^67^ The Bernal framework highlights that most interventions are not generalisable to ethnic/minority populations and, thus, need contextual adaptation to reflect the broader social, economic and political contexts of intervention.^66 68^ The framework consists of eight dimensions of treatment interventions—language, persons, metaphors, content, concepts, goals, methods and context—that guide the development of culturally sensitive treatments and the adaptation of existing psychosocial treatments.^65^ During this adaptation, we will also consider implementation factors and sustainability outcomes. The final PM+Adherence intervention manual will consist of five adapted and two adherence-focused sessions with corresponding material.

#### Cognitive interviewing

A bilingual research assistant will translate the intervention material to IsiZulu, followed by cognitive interviewing. Cognitive interviewing exercises ensure the materials are easily understood, acceptable and relevant to the population.^69 70^ Following a semi-structured guide, the Youth Advisory Board, comprising ALHIV aged 16–19 years from the community, will be invited to give feedback on the adapted PM+Adherence intervention materials and give input on whether they are relevant, understandable or acceptable.^70^

#### Psychologist read-through

An expert clinical psychologist will review the adapted intervention to ensure consistency and appropriateness of the adapted intervention manual and corresponding materials. The psychologist will use an existing glossary of mental health idioms and terminology from South Africa to guide the process.

### Phase 3: feasibility trial of the co-adapted PM+Adherence

#### Study design

In this phase, we will conduct a hybrid type 3 implementation study informed by the new NIHR and UK Medical Research Council framework for complex interventions^71 72^ to determine whether implementing the co-adapted intervention is appropriate for further testing and whether the ideas and findings can be shaped as relevant and sustainable.^73^,^75^

#### Study population

We will recruit adolescents (target sample size n=50) living with HIV and receiving care at AHRI-supported clinics. A random sample of 67 potential participants (ensuring gender balance) who are aware of their HIV status and have agreed to future contact with the AHRI team will be selected from the existing AHRI Demographic Information System (ACDIS) database, and they will be approached and invited to enrol. Adolescents will be included in the study if they are aged 16–19 at the time of recruitment, reside in uMkhanyakude at the time of recruitment, have a score of ≥10 on the Patient Health Questionnaire (PHQ-9) or Generalised Anxiety Disorder Scale (GAD-7) and provide informed consent. We will exclude individuals with a self-reported history of severe mental illness, including psychotic-related disorders, bipolar disorders, eating disorders and substance dependence, as well as those with cognitive deficits (assessed using the Mini-Mental Status Examination),^76^ those presenting with suicidal ideation or judged to be at active risk of suicide (as assessed using the Columbia-Suicide Severity Rating Scale), and those undergoing active psychiatric treatment (ie, on psychotropic medication or receiving formal psychotherapy).

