### Risk assessment and management

During screening, any potential participant identified as experiencing suicidal ideation using the Columbia Suicide Severity Rating Scale will be referred for further clinical/risk assessment by an AHRI clinical psychologist. The clinical psychologist will assess whether these are significant by considering a range of well-established factors, including history of suicidality, number of prior attempts, intention and plans. The psychologist will then decide whether they can continue with the study or require more specialised services. Although this study will not include them, we will link them with the appropriate services. Those identified with other challenges, in line with the AHRI Child Protection Standard, will be linked with the Child Protection Lead at AHRI for assessment, who will advise on further management where possible. Adverse events and serious adverse events will be closely monitored during each visit. In consultation with the Child Protection Lead, the principal investigator will determine whether these events may be related to the study and report to mentors, who will function as a monitoring board when necessary. The research assistants and facilitators will record and report these events to the study team, and serious adverse events will be reported to the ethical review committee.

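### Adolescents with suicidal ideation at screening are excluded outright in one section, while another leaves a psychologist to decide whether they continue; the two must be reconciled into one eligibility rule

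*Protocol article*

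**What the plan says.** The Study population section lists the Phase 3 exclusions. Among them are "those presenting with suicidal ideation or judged to be at active risk of suicide (as assessed using the Columbia-Suicide Severity Rating Scale"). The two conditions are joined by an 'or', and no clinical override is given.

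The Risk assessment and management section describes what happens at screening: "any potential participant identified as experiencing suicidal ideation using the Columbia Suicide Severity Rating Scale will be referred for further clinical/risk assessment". The assessor is a clinical psychologist. Two further steps follow: "The clinical psychologist will assess whether these are significant by considering a range of well-established factors", and then "The psychologist will then decide whether they can continue with the study or require more specialised services". The next sentence is: "Although this study will not include them, we will link them with the appropriate services".

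The Intervention subsection under Study procedures gives the enrolment step. It enrols on a score of 10 or more on the PHQ-9 or GAD-7 and does not mention the Columbia scale.

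**The concern.** Two sections govern the same decision for the same adolescents and can give different answers. Under Study population, ideation on the Columbia scale is enough to exclude. Under Risk assessment and management, ideation triggers a referral, and continuing in the study is one of its named outcomes.

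Three things depend on the answer.

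- **Who receives the intervention.** Entry requires a raised depression or anxiety score, so screening selects for distress. Lay counsellors deliver the sessions at the participant's home or elsewhere. Whether an adolescent with ideation may enter should not depend on which section staff consult.
- **Who makes up the sample.** The feasibility results and the before-after comparisons describe a different population under each reading.
- **Reach, a primary outcome.** Study outcomes defines it as the number of approached adolescents who are enrolled, so an eligibility rule that shifts enrolment shifts the numerator.

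**Working it through.** The document gives no figure for this point, so the main check is a comparison of the texts.

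**Same people, stage and instrument?** Yes. Study population sets entry criteria. The Risk assessment paragraph opens with screening and speaks of potential participants. Both name the Columbia scale, and both are triggered by ideation.

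**Outcome by type of adolescent, all otherwise eligible**

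| Finding at screening | Study population | Risk assessment, if the pronoun covers everyone with ideation | Risk assessment, if it covers only those needing specialised services |
|---|---|---|---|
| No ideation, no active risk | Eligible | Eligible | Eligible |
| Ideation, needs specialised services | Excluded | Excluded | Excluded |
| Ideation, cleared by the psychologist | Excluded | Excluded, so the decision just given to the psychologist has no effect | May continue |

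Only the third row is in dispute. On the broad reading, the Risk assessment section agrees with Study population but cancels its own preceding sentence. On the narrow reading, it is coherent in itself but contradicts Study population. Neither reading lets every sentence stand.

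**Does another section settle it?** No. The enrolment step in the Intervention subsection is silent on the Columbia scale.

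**Effect on reach.** Inputs: 67 approached and 50 enrolled (Sample size); a criterion of at least 75% (Table 2).

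- Planned reach = 50/67 = 74.6%.
- Shift for k adolescents in the third row = k/67. For k = 1 this is 1.5 percentage points; for k = 2, 3.0; for k = 3, 4.5.
- 75% of 67 is 50.25, so 50 enrolled falls just short and 51 (51/67 = 76.1%) meets it. One adolescent can therefore decide the criterion if enrolment is near plan.

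**How large is k?** It equals the number with ideation among those otherwise eligible, multiplied by the fraction the psychologist clears. The document gives neither quantity, so k cannot be computed.

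**The case against.** The strongest reply is that the Risk assessment section is coherent on its own. The psychologist sorts people into two groups, and the following sentence refers to the nearer one, those needing specialised services. That reading is natural and may be the intended one. It removes the conflict inside that section but not the conflict with Study population, which still excludes the adolescents who were cleared.

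A softer reply is that Study population is the summary and Risk assessment the operating procedure, so that only significant ideation excludes. This needs words that are not there: active risk is already a separate alternative in the exclusion, which leaves ideation sufficient by itself. Nor can the decision to continue be confined to enrolled participants who develop ideation later, because the paragraph is expressly about screening, and Table 1 schedules no Columbia assessment at later visits.

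Some stronger inferences are tempting, and the document does not support them.

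- **That safety handling itself is contradictory.** Referral and linkage to services appear only in Risk assessment and management, and nothing in Study population contradicts them. What differs is enrolment, and through it receipt of the intervention.
- **That the denominator of reach also moves.** The 67 are approached before screening, so on the Study outcomes definition only the numerator can change.
- **That a sizeable share of screen-positives changes status.** The document gives no frequency of ideation. Even with an assumed one, counting everyone with ideation would give only an upper bound, since those sent to specialised services are outside the study on every reading.

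**Conclusion.** The contradiction stands, in a narrow form. An otherwise eligible adolescent who reports ideation on the Columbia scale and is cleared by the psychologist is ineligible under Study population but may be enrolled under Risk assessment and management. The ambiguous pronoun leaves the second section unable to settle the matter.

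Each such case moves reach by about 1.5 percentage points, assuming that 67 are approached as planned and that reach is enrolled over approached. The number of cases is unknown. The finding does not depend on it: the conflict is in the wording of an eligibility rule, and fuller documents could not remove it without changing one of the two sections. The review takes no view on which rule is clinically right.

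**What to change.** The clinical team should decide on one eligibility rule for adolescents with suicidal ideation at screening. Then:

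1. Word Study population and Risk assessment and management to state that rule, and say plainly which group the study will not include.
2. Bring the enrolment step in the Intervention subsection into line, so that it no longer reads as though the PHQ-9 or GAD-7 score alone settles enrolment.
3. Use the same wording in all screening and risk documents.

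Reporting how many adolescents were referred and what became of them would be a useful addition. It does not replace the single rule, because the enrolled count would still depend on whether cleared adolescents may enter.

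The cost is a clinical decision and wording in three places, with no change to sample size, assessments or analysis.

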#### Participant timeline

Participants will be involved in the study for 6 months. Participants will complete assessments at baseline before the intervention is delivered. The intervention will be delivered over approximately 4 months, with sessions held every fortnight at the participant’s home or elsewhere. The decision to have the sessions fortnightly was due to expert feedback from local clinicians who indicated that every week would be burdensome to the young people as they need to also attend school in between clinic appointments. After completion of the intervention, participants will be scheduled for follow-up assessments at the endpoint (month 4) and 2 months post-intervention (month 6).

#### Training

Two types of training will be conducted in preparation for implementing the adapted PM+Adherence intervention. One is for research assistants (3), and another is for the intervention facilitators and lay counsellors (5). Research assistants will support the implementation of the study, including participant recruitment, collecting informed consent and outcome assessments. The research assistants will be individuals between the ages of 24 and 30 years, with a minimum bachelor’s degree, fluent in isiZulu. The research assistants’ training will cover the study’s background, methodologies, expected benefits and potential risks to participants, outcome assessment tools, administration of questionnaires and interviews, electronic data capture tools, the importance of data quality and consenting procedures. This training will be performed with the support of the AHRI Data Management team. The research assistants will also be trained on how to assess for risk, as well as monitor and record adverse and serious adverse events. For facilitators (lay counsellors) who deliver the PM+Adherence intervention, two pieces of training will be carried out in preparation for implementation. A 2-week training of trainers (ToT) workshop will be held for two trainers (both psychologists) to consider isiZulu language adaptations. The trainers will conduct supervised practice (role-play) and qualitative feedback will be collected during a debriefing session after training. A 3-month training of lay counsellors will follow ToT training. This length of time was based on previous studies using lay counsellors. The lay counsellors will be individuals between the ages of 24 and 30 years, with a minimum of matric (in South Africa, this is the grade 12 high school graduation certificate), lived experience of HIV or mental illness, from the local community with previous experience in community engagements/support. The training of lay counsellors will involve a combination of classroom and field support, followed by supervised practice in which facilitators will deliver the intervention to young people. The trainers will rate lay counsellors on fidelity and competency (ie, whether they completed each component of the session, how well they delivered the session, use of group facilitation skills, basic helping skills and how to manage acutely distressed participants). Lay counsellors will also be trained to complete self-report fidelity checklists of the intervention components. The intervention will be delivered face to face. They will also be trained to assess for risk and monitor and record adverse and serious adverse events. All research assistants and lay counsellors will be trained in safeguarding participants. The Ensuring Quality in Psychological Support platform will be consulted to select appropriate assessment tools, including WeACT–Foundational Helping Competencies for Children and Adolescents and the PM+ Competencies assessment tool.^77^

#### Study procedures

A research assistant will introduce the study, the purpose, what participation in the study involves, the length of participation, a reminder that participation is voluntary and that they can withdraw at any time without impacting their healthcare. Where possible, this will be done through a face-to-face conversation about the study; however, if this is not possible, the information will be sent via a medium (ie, email, WhatsApp) that the young person chooses and a method that will protect their privacy. Where there is a need for clarification, the research assistant will provide clarification in person or over the telephone. Potential participants will then be given time (no less than 48 hours) to look at the information sheets and ask questions about the study. The consenting process will be conducted in the participant’s native language (isiZulu) to ensure clarity and comprehension. The information sheets and consent forms will be periodically reviewed and revised as required throughout the study, such as when new safety data emerge. If changes are significant, participants will be approached for reconsenting accordingly.

##### Intervention

After informed consent, eligible individuals will be screened using the PHQ-9 and GAD-7. Individuals with a score ≥10 on the PHQ-9 or GAD-7 will be enrolled in the study and will complete a set of baseline assessments (table 1). After completing the baseline assessment, they will be assigned a lay counsellor and a date for their first interaction. Only trained lay counsellors who have undergone the proposed 3-month training will deliver the adapted PM+Adherence intervention for seven sessions held once a fortnight over 4 months.

**Table 1 T1:** Assessment schedule

	Baseline (month 0) (t_0_)	End intervention (month 4) (t_1_)	Postintervention (month 6) (t_2_)
Demographics	X		
Viral suppression	X		X
Adherence	X	X	X
PHQ-9	X	X	X
GAD-7	X	X	X
Sleep disturbance	X	X	X
PROMIS	X	X	X
CYRM	X	X	X
PWS	X	X	X

CYRMChild and Youth Resilience MeasureGAD-7Generalised Anxiety Disorder ScalePHQ-9Patient Health QuestionnairePROMISPatient-Reported Outcomes Information System Sleep Disturbance ScalePWSPersonal Well-Being Score

##### Drop-outs

Prior to the start of the intervention, contact details of the adolescent and a significant other (caregiver/friend) will be collected. During the intervention, if a participant misses a scheduled intervention session, the research staff will contact them by phone (up to three times before they are considered lost to follow-up) to book an alternative appointment to enhance retention. Our adoption criteria is at least ≥50% of sessions attended. At the end of the intervention, to understand the reasons for participant drop-out, we will make two attempts to call or visit participants who did not complete the intervention at home.

### Study outcomes

The primary outcomes of interest include (1) reach, which consists of how many of the approached ALHIV are enrolled in the study; (2) adoption and retention, which will assess the number of enrolled participants who attend ≥50% of sessions and undergo the final assessment at 6 months; (3) acceptability of the co-adapted intervention to determine how well the target population will receive the adapted intervention, the extent to which the intervention components meet the needs of the target population and the setting and (4) implementation, which will assess fidelity to the various elements of the intervention’s protocol, including consistency of delivery as intended as well as the adolescents’ use of the intervention strategies.

